
#### 2.9.2. Secondary and Exploratory Analyses

(i) Moderation (H4): the scenario × AI familiarity (B1, centered) interaction, via repeated-measures ANCOVA or a linear mixed model with random intercepts per participant, the recommended framework for vignette data [62]; presentation sequence is retained as a between-subjects factor here, as in every repeated-measures model in this protocol. (ii) Person-level multiple regression: mean acceptability across scenarios predicted by AI familiarity, general AI attitudes, and demographics (reporting *B*, *SE*, β, 95% CI, R^2^, VIF). (iii) Responsibility migration (H3): a 4 × 4 mixed ANOVA (scenario × actor, RES1–RES4, both within-subjects; presentation sequence between-subjects) with Greenhouse–Geisser correction; the scenario × actor interaction is the direct test of H3. Because H3 is confirmatory, it receives the same order controls as H1 and H2: the sequence terms are inspected first, and the migration estimate is repeated in a linear mixed model containing an additive serial-position term. (iv) Responsibility concentration: a normalized Herfindahl–Hirschman index computed per scenario from the relative weights of the three responsible actors (surgeon, hospital, AI developer; RES4—unavoidable medical uncertainty—is not a responsible actor and is analyzed separately), compared across scenarios by mixed repeated-measures ANOVA with sequence as a between-subjects factor; low values index diffusion of responsibility across actors, operationalizing the “problem of many hands” described in the responsibility literature [44,45]. (v) RES5 (moral duty) and RES6 (outcome-independent accountability): mixed repeated-measures ANOVAs across scenarios with sequence as a between-subjects factor, Holm-corrected within the family. (vi) Global preference (P1): a goodness-of-fit chi-square with standardized residuals over six analysis categories on 5 degrees of freedom. The six categories are the four scenarios, “I would prefer AI not to be involved in any way,” and a combined “no clear preference” category; the last pools the item’s two undecided options (“I have no preference” and “I cannot decide”), which are combined a priori because neither expresses a preference between scenarios and each is expected to be sparse. Consistency between stated preference and each participant’s maximum-acceptability scenario is reported descriptively. (vii) Exploratory: P4a and P4b (the surgeon’s permanent legal and, separately, moral responsibility) analyzed descriptively, compared with each other by a dependent-samples test on the within-person difference, and correlated with RES5/RES6; free-text concerns (P2) summarized by brief thematic analysis. (viii) Sensitivity analyses: primary analyses repeated (a) excluding participants with a single attention-check failure (who are retained under the primary rule) and (b) excluding participants with any comprehension failure, to demonstrate that conclusions do not depend on the cleaning criteria [69]. (ix) Order effects: descriptive profiles by sequence, the scenario × sequence interaction with its effect size and 95% confidence interval, and sequence-specific manipulation-check profiles. (x) Response-pattern typology (exploratory): where the random-slope test of Section 2.9.1 indicates heterogeneity, individual acceptability trajectories across autonomy levels are classified by latent-class growth analysis, with class enumeration by BIC and entropy and a minimum class size of 5% fixed in advance, and class membership described against AI familiarity, healthcare-system trust, and demographics; no inferential claim is attached to this analysis. (xi) Healthcare-system trust (B6) enters the person-level regression of (ii) as a covariate and is examined as an exploratory moderator of the autonomy effect, alongside healthcare contact frequency (B5) and prior surgical experience (B4, B4a). (xii) Subgroup analyses, all of which are secondary or exploratory, are governed by a minimum-cell rule fixed in advance: inferential tests within a subgroup are reported only where that subgroup contains at least 50 valid participants, the size at which a within-subject difference in *dz* = 0.40 is detectable at power 0.80; subgroups of 30–49 are reported descriptively with 95% confidence intervals and labeled as underpowered; subgroups below 30 are pooled into a residual category or not reported. A difference between subgroups is never inferred from a significant effect in one and a non-significant effect in another; only the formal interaction term, with its own confidence interval, supports such a claim. The set of moderators is fixed a priori, in the pre-registration, to seven: AI familiarity (B1), healthcare-system trust (B6), healthcare contact frequency (B5), prior surgical experience (B4/B4a), education (D3), age (D2), and field of activity (D4). Results are reported for all seven irrespective of significance, and no further moderator is added after the data are seen. (xiii) Missing data: because all closed items are mandatory, missingness in the dependent variables is structurally impossible within a submitted questionnaire. Two other forms of missingness remain. The first is unit-level, from questionnaires abandoned before submission. The platform is configured not to store partial submissions, so responses from abandoned questionnaires are neither retained nor analyzed (Section 2.10 and Appendix A.1). Attrition is therefore characterized from the platform’s page-level counters—how many participants reached each page—rather than from partial response data, and is reported as drop-out by serial position in the participant-flow diagram. Analyses are accordingly restricted to complete cases, that is, participants with all four scenario blocks, and no imputation is performed: with no partial records retained, there are no incomplete cases to impute. The second is item-level, on the background and demographic items that offer a “prefer not to answer” option or, in the case of B4 and B4a, are not displayed where the explicit health-data consent is declined; these are treated as a distinct category descriptively and as missing in inferential models, with a sensitivity analysis retaining the category in the person-level regression. Because complete-case analysis is not neutral when attrition is differential, drop-out is compared across the four presentation sequences, and any imbalance is reported and carried into the interpretation of the order analyses. All tests are two-tailed at α = 0.05, with exact *p*-values, effect sizes, and 95% confidence intervals reported for all tests, including non-significant ones. On closed 1–7 scales, no distribution-based outlier removal is applied.

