### 1.2. Public Attitudes Toward Medical AI

A substantial body of the recent literature has characterized public and patient attitudes toward clinical AI. Syntheses converge on a consistent pattern: the public is broadly receptive to AI as a support tool but insists on human involvement and personalized care [21,22]. Large surveys find that most patients expect AI to improve care while reporting substantial concerns about misdiagnosis, privacy, and the erosion of the patient–clinician relationship [23], that comfort is conditional on physician supervision of the final decision [24,25], and that trust is lowest precisely for surgical applications [26]. Experimental work shows that acceptance of AI-based care rises when physicians endorse and explain the system [27,28], and that patients react negatively when AI use is not disclosed or when AI and clinician recommendations conflict [29,30]. A recent multinational hospital survey spanning 43 countries confirmed predominantly favorable views combined with a marked preference for explainable, physician-supervised AI [31]. Within surgery specifically, patients presenting to a surgical clinic reported low familiarity with and limited trust in AI involvement in their care [32], and users evaluating AI-enabled decision aids valued them for shared decision-making rather than autonomous decision-making [33]. Vignette-based population experiments identify system reliability and transparency as the leading drivers of support [34], and AI familiarity, education, and health literacy recur as determinants of acceptance [35,36].

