### 1.6. Objectives and Hypotheses

The primary objective is to evaluate the attitudes of Romanian adults recruited online—acceptability, trust, risk perception, and responsibility attribution—toward four progressive scenarios of AI implementation in facial reconstructive surgery. The secondary objectives are (i) to analyze the moderating effect of AI familiarity on acceptability across autonomy levels; (ii) to investigate how responsibility attribution (surgeon, hospital, AI developer, unavoidable medical uncertainty) varies across scenarios; (iii) to explore the moral–legal distinction in responsibility attribution; (iv) to identify the preferred model of AI implementation in facial reconstructive surgery; and (v) to quantify the influence of presentation sequence on all primary outcomes and to estimate the autonomy effect adjusted for serial position.

Four hypotheses will be tested. H1. Acceptability and trust decrease significantly as the level of AI autonomy in the surgical decision increases. H2. Perceived risk increases as human control over the decision process decreases. H3. Responsibility attribution shifts progressively from the surgeon toward the AI developer as algorithmic autonomy increases. H4. Prior familiarity with AI moderates the relationship between implementation scenario and acceptability, such that participants familiar with AI show a smaller decline in acceptability for high-autonomy scenarios; H4 is treated as partially exploratory, given the power constraints described in Section 2.5. H1–H3 fix the expected direction but not the functional form: each is tested by an omnibus effect of autonomy level followed by the full set of orthogonal polynomial contrasts, so that threshold-like or otherwise non-monotonic patterns are detected rather than forced into a linear trajectory (Section 2.9.1). A design-validation hypothesis is tested alongside them, namely that responses do not depend on the sequence in which the scenarios were presented; it is evaluated as the scenario × sequence interaction, and a non-null result is treated as evidence of order dependence to be reported and adjusted for, not as a substantive finding about autonomy.

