### 2.6. Instrument and Measures

The instrument is a structured online questionnaire originally developed for this study, administered in Romanian in a single version distributed through a single link; the complete instrument (English translation) is reproduced in Appendix A. It comprises twelve sections: (1) informed consent and eligibility screening; (2) background and prior experience—AI familiarity (B1), experience with AI tools (B2), confidence in understanding medical information (B3), prior surgery and prior face/head/neck surgery (B4, B4a), healthcare contact frequency (B5), and trust in the national healthcare system (B6); (3) general attitudes toward AI in medicine (G1–G4, with G2 and G4 reverse-keyed for any composite); (4) the first attention check; (5–8) the four scenario blocks, administered in the sequence to which the participant was randomly allocated, each consisting of a vignette, a comprehension check, and an identical response block; (9) overall preferences and acceptability (P1–P4b); (10) the second attention check; (11) demographics (D1–D7: gender, age, education, occupational field, subjective financial situation, residence environment, development region); and (12) closing debriefing.

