H4. moderation by AI familiarity (partially exploratory)	RM-ANCOVA or linear mixed model with random intercepts: scenario (within) × B1 (centered), sequence between	F (or likelihood-ratio test), *p*, *f*^2^; simple slopes with 95% CI
Global preference (P1)	Goodness-of-fit chi-square over 6 analysis categories (2 undecided options pooled); standardized residuals; consistency with maximum-acceptability scenario, descriptive	χ^2^, *df*, *p*, *w*; standardized residuals
Predictors of acceptability	Person-level multiple regression: mean acceptability on familiarity, general attitudes, demographics	*B*, *SE*, β, 95% CI, R^2^, VIF
P2, P4a/P4b (exploratory)	Brief thematic analysis (P2); descriptive statistics, within-person P4a–P4b difference, and correlations with RES5/RES6	Theme frequencies; Pearson/Spearman *r*
Order dependence (design validation)	Scenario × sequence interaction in the mixed RM-ANOVA; position-adjusted linear mixed model (autonomy + serial position, random intercepts)	*F*, corrected *df*, *p*, partial η^2^ (90% CI); adjusted vs. unadjusted scenario means
Functional form of the autonomy effect	Orthogonal polynomial contrasts (linear, quadratic, cubic); Holm-corrected adjacent-pair contrasts	*F*, *p*, partial η^2^ per contrast; share of the omnibus effect
Autonomy vs. technical complexity	Mixed RM-ANOVA on MAN2 (sequence between); primary models re-estimated with MAN2 as a time-varying covariate	*F*, corrected *df*, *p*, partial η^2^; adjusted scenario means
Between-person heterogeneity (exploratory)	Random-slope linear mixed model; latent-class growth analysis of individual trajectories	Likelihood-ratio χ^2^, *p*; random-slope SD; class sizes, BIC, entropy

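### H4 tests scenario × AI familiarity without age, education or B3 by scenario, so a positive result would describe familiar respondents but could not be credited to familiarity itself

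*Protocol article*

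**What the plan says.** H4 (section 1.6) states that "participants familiar with AI show a smaller decline in acceptability for high-autonomy scenarios". Secondary objective (i) calls this a moderating effect of AI familiarity.

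The model is given twice, consistently. Section 2.9.2(i) has "Moderation (H4): the scenario × AI familiarity (B1, centered) interaction, via repeated-measures ANCOVA or a linear mixed model with random intercepts per participant" and retains sequence. Table 5 has "RM-ANCOVA or linear mixed model with random intercepts: scenario (within) × B1 (centered), sequence between". Neither names age, education or B3, as a main effect or by scenario.

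Three other places come close:

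- Section 2.9.2(ii) puts familiarity and demographics in one model: "Person-level multiple regression: mean acceptability across scenarios predicted by AI familiarity, general AI attitudes, and demographics". Its outcome is the average over the four scenarios.
- Section 2.9.2(xii) says "The set of moderators is fixed a priori, in the pre-registration, to seven". Besides B1, B5 and B6, the list holds "prior surgical experience (B4/B4a), education (D3), age (D2), and field of activity (D4"). All seven are to be reported whatever their significance, and none may be added once the data are seen. The text does not say that they enter one model together.
- Section 2.6 collects "confidence in understanding medical information (B3"), the item nearest to health literacy. It is not among the seven.

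Section 1.2 names the neighbouring traits: "AI familiarity, education, and health literacy recur as determinants of acceptance". The cautions attached to H4 (sections 1.6, 2.5 and 3) concern power only.

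**The concern.** Scenario is manipulated within person and its order is randomised, so scenario contrasts are well protected. Familiarity is not manipulated. A scenario × B1 interaction compares the declines of different kinds of people, and the within-person design removes only differences in level between them. If a trait that travels with familiarity changes how steeply acceptability falls, scenario × B1 picks up part of that trait's effect. Main-effect covariates do not remove it; only trait × scenario terms do.

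At stake is the wording of the H4 conclusion. A result supporting H4 could be read as familiarity buffering the reaction to autonomy, when the data fit equally well with, say, younger respondents reacting less. The regression in (ii) cannot settle this because its outcome contains no decline. One-at-a-time moderator tests under (xii) would show that rivals exist, but not whether the B1 interaction survives them.

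**Working it through.** **The plan's own figures.** Inputs from section 2.5 and Table 2: N = 300, 3 df, α = 0.05, power 0.80. With noncentral F, numerator df 3, denominator df N − 4 and λ = N·f², the minimum detectable interaction is f² = 0.0368 (stated 0.037), and f² = 0.02 needs N = 550 (stated ≈ 550). Both reproduce, so the same formula is used below.

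**Assumptions, none of them in the documents.** Familiarity has no moderating effect of its own. One other trait moderates the decline and explains a share R² of its variance, so the trait's f² = R²/(1 − R²). The trait correlates r with B1.

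**Formula.** The share of variance that B1 picks up is r²R². Hence f² for B1 = r²R²/(1 − r²R²) and λ = 300 × that f². The rejection rate is the probability that F(3, 296; λ) exceeds its 5% critical value, 2.635.

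**Trait effects of the size used in the plan's own power section:**

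| Trait f² | R² | r | r²R² | λ | Rejects |
|---|---|---|---|---|---|
| 0.02 | 0.0196 | 0.3 | 0.0018 | 0.53 | 8% |
| 0.02 | 0.0196 | 0.4 | 0.0031 | 0.94 | 11% |
| 0.037 | 0.0357 | 0.3 | 0.0032 | 0.97 | 11% |
| 0.037 | 0.0357 | 0.4 | 0.0057 | 1.72 | 17% |

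**Larger trait effects, r = 0.4:**

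| R² | Trait f² | r²R² | λ | Rejects |
|---|---|---|---|---|
| 0.05 | 0.053 | 0.008 | 2.42 | 22% |
| 0.10 | 0.111 | 0.016 | 4.88 | 43% |
| 0.15 | 0.176 | 0.024 | 7.38 | 61% |

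**Simulation check.** At N = 300 with 2,000 runs per setting and trait f² = 0.037, the unadjusted test rejected in 11% (r = 0.3) and 17% (r = 0.4) of runs. With r = 0 it stayed at 4–6% for all trait sizes tried (f² = 0.037, 0.08, 0.15). With trait × scenario added it returned to about 4–6% in every setting.

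**Precision cost of adjusting.** The standard error of the B1 interaction grows by 1/√(1 − R_B²), where R_B is the multiple correlation of B1 with the added traits:

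- R_B = 0.3: 1/√0.91 = 1.05
- R_B = 0.4: 1/√0.84 = 1.09
- R_B = 0.5: 1/√0.75 = 1.15

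Keeping 80% power at f² = 0.037 would need 300/(1 − R_B²) participants: 334, 375, 429 or 500 if the traits explain 10%, 20%, 30% or 40% of B1.

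**Data availability.** Section 2.7 makes all closed items mandatory and allows a refusal option only for B4, B4a, B5, B6, D1, D6 and D7. B1, B3, D2 and D3 are therefore complete in every submitted record.

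**The case against.** The strongest reply is that H4 compares people, not causes. If age drives the decline and goes with familiarity, familiar respondents really do decline less, H4 as worded is true, and the rejections counted above are correct ones. This stands. A reader might infer that the planned test has an inflated error rate, or that the study would name the wrong moderator. The documents do not support that, since they never claim an effect of familiarity holding other traits fixed. The percentages are error rates only for that conditional reading.

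Second, section 1.2 speaks of determinants of acceptance, which is level, and does not name age. Nothing in the article shows that these traits change the decline. This also stands, and it is why the concern is conditional. A reader might take 22–61% as the expected size; those figures assume trait effects above the plan's own 0.02 and 0.037.

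Third, age and education interactions will be reported under (xii), Table 4 lists B2–B5 and D1–D7 as covariates or sample description, and a separate analysis plan is to be deposited. This helps only in part. Rivals will be visible for two of the three traits, but separate tests do not disentangle correlated traits, the H4 row of Table 5 names no covariate, and B3 has no scenario interaction in the article.

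Fourth, H4 is partially exploratory and already short of power, so adjustment weakens it further. This is a good argument against making the adjusted result a hurdle, but not against reporting it.

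**Conclusion.** The point holds in a limited form. The planned H4 interaction is valid as a description of familiar versus unfamiliar respondents. It does not support attribution to familiarity itself if age, education or B3 both correlates with B1 and alters the decline, and no analysis stated in the article would tell the two apart.

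The size is unknown because the documents give neither link. Under the stated assumptions, rejection with no effect of familiarity's own is about 8–17% at the plan's own effect sizes and r = 0.3–0.4, and reaches 22–61% only for trait effects explaining 5–15% of the variance in the decline at r = 0.4. H1–H3 and every stated figure are unaffected. This is a cheap improvement, not a defect that undermines the study.

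**What to change.** Keep the planned H4 model in section 2.9.2(i) and Table 5. Beside it, pre-specify one sensitivity model that adds scenario × D2 (age), scenario × D3 (education) and scenario × B3. Report the B1 interaction with its confidence interval from both, as section 2.9.1 already does for position-adjusted and unadjusted estimates. Word H4 as an association unless the adjusted estimate is similar in direction and size. Do not require the adjusted term to be significant, because the test is already short of power.

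State in the pre-registration that B3 enters as an adjustment term and not as an eighth moderator. Added later, it would be a declared deviation.

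The cost is one extra model on items already collected, with no participant lost, and a wider interval for the adjusted B1 term: about 5%, 9% or 15% larger standard error if the traits jointly have multiple correlation 0.3, 0.4 or 0.5 with B1, and more if it is higher.

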The per-scenario response block contains nine Likert items measuring the three primary dependent variables—acceptability (ACC1–ACC3), trust (TRU1–TRU3), and perceived risk (RSK1–RSK3)—followed by six responsibility items (RES1–RES4: surgeon, hospital, AI developer, unavoidable medical uncertainty; RES5: the surgeon’s moral duty to verify AI outputs; RES6: outcome-independent accountability), two manipulation-check items (MAN1: perceived AI control over the final surgical decision; MAN2: perceived technical sophistication of the system), and a perceived difficulty item (DIF1). All scaled items use 7-point end-anchored Likert response formats. Composite scores are computed as the arithmetic mean of their items after reverse-scoring RSK1 (8 − score), which is the only reverse-keyed item in the response block; higher risk scores indicate higher perceived risk. Treating item means on end-anchored 7-point scales as quasi-continuous interval variables is standard practice in experimental vignette research; ordinal-model sensitivity analyses are nevertheless planned in line with current guidance on Likert-based outcomes [62,71]. Table 4 summarizes the measurement structure; per-scenario variables carry the scenario suffix (e.g., ACC1_A, ACC1_B, ACC1_C, ACC1_D).

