
### 2.9. Statistical Analysis

#### 2.9.1. Primary Analyses

Each composite score (acceptability, trust, perceived risk) will be analyzed by a mixed repeated-measures ANOVA, with autonomy level (four scenarios) as the within-subjects factor and presentation sequence (four Williams sequences) as the between-subjects factor. The Greenhouse–Geisser correction will be applied when Mauchly’s test indicates a sphericity violation (Huynh–Feldt for ε between 0.75 and 1), and the multivariate approach (Pillai’s criterion) will be reported in parallel as a sphericity-robust check. H1 and H2 will be tested with within-subjects trend contrasts across the autonomy gradient. Because acceptance need not fall in a straight line, the complete set of orthogonal polynomial contrasts—linear, quadratic, and cubic—is pre-specified, and each is reported together with the proportion of the omnibus effect it accounts for. A purely linear profile leaves the quadratic and cubic components negligible, whereas a step between two adjacent levels appears as a large linear component accompanied by a substantial quadratic or cubic one. Because every monotone step is linear-dominant, the polynomial decomposition establishes departure from a straight line but cannot by itself locate the break; the break is identified only from the Holm-corrected adjacent-pair contrasts (A–B, B–C, C–D). A quadratic-dominant profile with a small linear component would instead indicate a non-monotone pattern, which the hypotheses do not predict and which would be reported as such. A non-monotonic or threshold pattern will be reported as such rather than summarized by the linear trend alone. Post hoc comparisons use dependent-samples *t*-tests for the six scenario pairs with Holm’s sequential correction, applied within each hypothesis-defined family of tests in line with current guidance on multiplicity control [74]. Effect sizes will be reported as partial η^2^ for omnibus tests and Cohen’s dz for pairwise comparisons, with 95% confidence intervals, following effect-size-centered reporting recommendations [64]. Assumption checks include graphical inspection of difference-score distributions; as a distributional robustness analysis, the Friedman test with Holm-corrected Wilcoxon signed-rank pairwise comparisons will be reported alongside each primary test—supplemented by ordinal (cumulative-link) models as sensitivity analyses for the Likert-based outcomes [71]—and the concordance of parametric and nonparametric conclusions stated explicitly. Order dependence is tested directly as the scenario × sequence interaction; a non-significant interaction, together with equivalence of the four sequence-specific profiles, supports pooling across sequences. Independently of that test, the autonomy effect is re-estimated from a linear mixed model with random intercepts per participant and additive fixed effects of autonomy level and serial position (1–4). The Williams square renders this model identified, so the estimate is adjusted for arbitrary—not merely linear—serial-position and fatigue effects, while first-order carry-over is balanced by the design rather than modeled; position-adjusted and unadjusted estimates are reported side by side, and any material divergence between them is treated as evidence of an order artifact and interpreted accordingly. Perceived difficulty (DIF1) and perceived technical sophistication (MAN2) are each added as time-varying covariates in further sensitivity models, addressing fatigue and the possibility that responses track the apparent complexity of the system rather than its autonomy. Finally, between-person heterogeneity in response profiles is examined by adding a random slope for the linear autonomy contrast and testing the improvement in fit by a likelihood-ratio test; a substantial random-slope variance indicates that an average trajectory conceals distinct response patterns and licenses the exploratory typology described in Section 2.9.2. Because a non-significant test is not evidence of absence, a smallest effect size of interest of *dz* = 0.20—the value detectable at the Bonferroni bound for the six pairwise contrasts at *N* = 300—is fixed in advance, and equivalence testing by two one-sided tests against that bound is reported alongside every null pairwise result, so that any claim that two adjacent scenarios do not differ rests on an equivalence test rather than on the absence of significance.

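### H4 is tested only on bounded 1–7 means, so scale compression can create or hide a scenario × familiarity interaction; the planned ordinal sensitivity model should be extended to H4

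*Protocol article*

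**What the plan says.** Section 1.6 states H4 with a direction: "participants familiar with AI show a smaller decline in acceptability for high-autonomy scenarios". It calls the hypothesis partially exploratory because of limited power.

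The test is fixed in two places. Section 2.9.2(i) gives "the scenario × AI familiarity (B1, centered) interaction, via repeated-measures ANCOVA or a linear mixed model with random intercepts per participant", and the H4 row of Table 5 gives "RM-ANCOVA or linear mixed model with random intercepts: scenario (within) × B1 (centered), sequence between". Both are linear models for the acceptability composite. Section 2.6 says "All scaled items use 7-point end-anchored Likert response formats" and scores each composite as the arithmetic mean of its items, so the outcome cannot leave the range 1 to 7.

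Ordinal models appear twice. Section 2.6 says in general that "ordinal-model sensitivity analyses are nevertheless planned in line with current guidance on Likert-based outcomes". Section 2.9.1 places them: rank tests accompany each primary test, "supplemented by ordinal (cumulative-link) models as sensitivity analyses for the Likert-based outcomes". Neither place names H4. The sensitivity analyses in Section 2.9.2(viii) also repeat only the primary analyses.

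The stated cautions on H4 (Sections 2.5 and 3) concern power: a non-significant result is not to be read as absence of an effect. They do not address a significant result that arises from the limits of the scale.

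**The concern.** A linear interaction on a bounded mean compares differences that the scale may have shortened unequally. Take two respondents whose underlying decline from A to D is 2 points. One moves from 5.5 to 3.5, a recorded decline of 2. The other sits two points higher and moves from 7.5 to 5.5; the first rating is capped at 7, so the recorded decline is 1.5. If the higher respondent is also the one more familiar with AI, the data show the pattern H4 predicts although both reacted identically.

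The same happens at the floor with the opposite sign. With an underlying decline of 4, a respondent moving from 4.5 to 0.5 is recorded as 4.5 to 1, a decline of 3.5. A respondent one point higher moves from 5.5 to 1.5 and shows the full 4.

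Two conditions are needed: a familiarity main effect, and scenarios that differ in how close they lie to an end of the scale. The protocol makes the first plausible, since Section 1.2 lists AI familiarity among recurring determinants of acceptance. For the second, Section 1.2 says that "the public is broadly receptive to AI as a support tool but insists on human involvement and personalized care", and Section 3 expects the largest drop at D. These statements allow a ceiling at A, a floor at D, or both. At stake is whether a significant H4 interaction, in either direction, can be read as familiarity changing the reaction to autonomy.

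**Working it through.** **1. The plan's own H4 figures.** Inputs from Section 2.5 and Table 2: N = 300, 3 numerator df, α = 0.05, power 0.80. Power = P[F′(3, v, λ) > F₀.₉₅(3, v)] with λ = f²·N. With v = N − 8 = 292, the detectable f² is 0.0368 (λ = 0.0368 × 300 = 11.04), against the stated 0.037. For f² = 0.02 the required N is 550 (λ = 0.02 × 550 = 11.0), as stated. Other choices of error df and noncentrality gave 0.0365–0.0373 and 547–554. The power figures are therefore right; they simply do not bear on this question.

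**2. Simulation without latent moderation.** Rating = scenario mean + person effect (including a B1 main effect) + person-by-scenario deviation + item error, rounded and clipped to 1–7, three items averaged, N = 300. No scenario × B1 term is present on the latent scale. The documents give no means, SDs or familiarity effect, so these are assumptions and were varied.

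*Set 1* (all three SDs 0.9; B1 effect 0.3 or 0.5 points per SD of B1, correlating about 0.28 to 0.48 with mean acceptability). The 3-df test has a nominal rate of 5%; the 1-df linear-trend contrast has 2.5% in each direction.

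| Observed means | 3-df test | Linear contrast |
|---|---|---|
| A 5.8–6.1, D 4.2–4.7 | 9–40% | 12–58% towards H4 |
| A 5.8, D near the floor | can exceed 5% | about 3–5% towards H4 |
| A 4.9, D 2.2 | can exceed 5% | 7–17% against H4 |
| Any of these, no B1 effect | – | about 5% two-sided |

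*Set 2* (latent SD 1.5, inter-scenario correlation 0.50, item SD 1.0; B1 effect 0.3/0.5/0.7 per SD).

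| Observed means | Linear contrast, towards H4 | Linear contrast, against H4 |
|---|---|---|
| A 6.0, D 4.0 (31% at 7 in A) | 21/46/76% | – |
| A 5.7, D 4.0 (21% at 7 in A) | 10/21/39% | – |
| A 5.3, D 3.5 (14% at 7 in A) | 4/8/12% | – |
| A 4.9, D 3.1 (symmetric) | about 2% | – |
| A 5.3, D 2.0 (31% at 1 in D) | 0.3/0.1/0.1% | 10/18/32% |

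For the first row the 3-df test rejects in 13/31/57% of runs. With no B1 effect the rate is nominal in every profile.

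One refinement: when A is near the ceiling and D equally near the floor (5.68 and 2.32), the linear contrast stays close to nominal (3–4% towards H4, about 2% against). The 3-df test still rejects in 8.0/13.2/21.5% of runs, because the middle scenarios are not compressed like the outer ones.

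**3. Does an ordinal model remove it?** The Set 2 model was refitted with an item-level cumulative probit and participant-clustered standard errors (B1 effect 0.5, 200 runs).

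- Latent A–D means 6.5/6/5.5/4: significance towards H4 falls from 48.5% to 1.5%; the 3-df ordinal test rejects in 6.0%.
- Latent means 6/5.5/5.25/4: from 20.5% to 3.0%; 3-df 6.5%.
- Latent means 5.5/4.5/4/1.5 (floor at D): significance against H4 falls from 23.5% to 2.5%; 3-df 7.5%.

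With 200 runs these ordinal rates are compatible with nominal or slightly above it.

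**The case against.** Several objections carry weight.

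- **Direction.** A reader might infer that the ceiling alone makes familiar respondents appear to decline less, so that H4 is bound to be supported. The documents do not support that. Without a familiarity main effect nothing happens, and with D near the floor the bias fades or reverses. Section 1.2 also reports that trust is lowest for surgical uses, Section 1.3 that aversion is strongest in consequential or embodied domains, and Section 4 low institutional trust in the region with no predicted direction. Ratings of A need not be high.
- **Which test.** The highest rates belong to a 1-df trend contrast. Table 2 plans a 3-df interaction, for which the rates are lower (46% against 31% in one setting). The 3-df figures are the ones to quote.
- **Table 5.** Its silence on ordinal models for H4 proves little, since the H1 and H2 rows list none either although Section 2.9.1 plans them. Section 2.6 promises ordinal sensitivity analyses in general, and a separate analysis plan is to be deposited. What remains is that the only section assigning these models ties them to the primary tests.
- **Functional form.** A reader might extend the argument to the expected C–D step. That is a primary analysis, for which ordinal sensitivity models are already planned, so it is not part of this point.
- **Estimand.** A difference in raw mean acceptability is a real difference on that scale. Requiring significance on the latent scale before any claim about H4 would impose one choice of estimand, and the documents give no ground for it.
- **Stakes.** H4 is secondary, partially exploratory, labelled so in every table, and to be interpreted with caution. This lowers the priority. It does not tell a reader what a significant interaction means, because the stated cautions concern low power.

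**Conclusion.** The point holds in a limited form. H4 is specified as a linear interaction on bounded means, and no ordinal or ceiling check is assigned to it. Given a familiarity main effect and scenarios at unequal distances from the ends of the scale, compression can produce a significant interaction without latent moderation. The planned 3-df test rejected in about 9–40% of runs, against 5%, at assumed A means of 5.8–6.1 and D means of 4.2–4.7, in the direction of H4. The bias runs against H4 when D is near the floor and A is nearer mid-scale. It is negligible for a symmetric mid-scale profile and without a familiarity main effect.

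These sizes rest on assumed means, SDs and familiarity effects, since the documents give none, and on defining moderation on a latent scale. They show that the artifact is possible within plausible ranges, not that it will occur. H1–H3 are not affected by this point. It is a cheap improvement to a secondary analysis.

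**What to change.** In Section 2.9.2(i) and the H4 row of Table 5:

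1. Extend the cumulative-link sensitivity analysis already planned for the Likert outcomes to the scenario × B1 interaction, allowing for repeated ratings within participant.
2. Report the share of ratings at 7 and at 1 by scenario and by familiarity level.
3. State that, where the raw-scale and ordinal results disagree, the H4 interaction is reported as scale-dependent rather than as clear support for moderation.

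The raw-scale test stays as the planned test; the ordinal result informs its interpretation and is not a condition for reporting it. The cost is one more sensitivity model and a sentence or two in the pre-registration, and some nominally significant H4 results will be described more cautiously. Section 2.12 says that pre-registration and data collection have not yet taken place, so the change can be made now without counting as a deviation.
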